Combining the successful results of G-COACH and the orthogeriatric care model abroad, we set up a care strategic project (2021-2024) for geriatric-surgical co-management within the University Hospitals Leuven, named **G-COMAN**. G-COMAN aims to optimize geriatric care in elderly surgical patients through a phased implementation of geriatric surgical co-management on the services traumatology, abdominal surgery and vascular surgery. This year (2021) is dedicated to pre-implementation. From 2022 onwards, G-COMAN will start implementing the program on the traumatology ward. Dedicated nurses will perform comprehensive geriatric assessments (CGA) in all patients aged 75 and older on the traumatology ward. By systematically organizing proactive care with collaboration and shared decision making between geriatric and surgical departments, postoperative care outcomes will hopefully improve.

This observational study will evaluate the **effectiveness of geriatric-traumatology** part of the G-COMAN program and will examine **which factors contribute to** a (non)successful **implementation** of the program as we aim to sustainable embed geriatric care aspects in the standard care of surgical services.

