### 3.3 Secondary endpoints

1) Effectiveness evaluation

The secondary endpoints include comparison between the two groups on **patient outcome**:

- Length of hospital stay

- quality of life: EQ-5D^10^ (at admission, discharge, 1 month, 3 months, 6 months and 12 months post-surgery)

- functional status: Parker Mobility Score^11^, modified Barthel Index^12^, Lawton and Brody Scale^13^, Katz index (admission, discharge, 1 months, 3 months and 6 months post-surgery).

- hospital readmissions (30 and 90 days after discharge)

- falls (= “an unexpected event in which the patients comes to rest on the ground, floor or lower level”) and new fractures, either by retrospectively checking electronic patient record for any contact after discharge to any hospital or emergency department stating the occurrence of falls or new fractures) and by a questionnaire send out to patient and care givers. (admission, in-hospital, at discharge, at 1, 3, 6 months post-surgery 12 months post-surgery)

- Living situation: defined in 5 categories: living alone at home, living with spouse/partner, living with children, assisted living, living in a facility with 24h care such as nursing home). Details of care provided will be recorded as one of the following categories: 24h care, daily, irregular, no care. (admission, discharge, 1 month, 3 months post-surgery, 12 months after surgery)

- mortality (in-hospital, 1 month post-discharge and 12 months after discharge)

- secondary fracture prevention: documentation of fall risk assessment, medication review of calcium/vitamin D use and osteoporosis treatment, appointment to fracture liaison service (12 months after surgery)

- nutritional status: Mini Nutritional Assessment (MNA) ^14^ (at admission, 1 month, 3 months and 6 months post-surgery)

- cost-benefit analysis:

Costs will be assessed using a model that registers key hospital activities from the electronic patient record (KWS): 'beeldvorming', 'daghospitalisatie', 'dialyse', 'functiemeting', 'hospitalisatie', 'hospitalisatie ITE', 'labo', 'operatiekwartier', 'paramedische staf', 'raadpleging', 'raadpleging functiemeting', 'radiotherapie', 'spoedgevallen'. The model was developed by UHL.

2. Feasibility evaluation (is the intervention successfully implemented?):

2.1:

- the reach of the program (% of all eligible patients that were included in the G-COMAN program, defined as the patients who completed the questionnaire)

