- use and duration of physical restraints (as registered in the electronic patient record; 3-points fixation or higher degrees of fixation)

- use and duration of indwelling catheters (urinary tract catheter or intravenous catheter as registered in the electronic patient record)

- Medication reconciliation at admission and discharge (calcium/vitamin D supplements and AOM)

- referral to geriatric day clinic (appointment to E459 in the year following first admission)

- Referral to fracture liaison services (Zoledronate infusion and/or metabolic bone consultation)

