| Quality of life | EQ-5D | Mobility, self-care, daily activities, pain, anxiety |  | Questionnaire | X | X | X | X | X | X | No |
| Medication | N/A | Use of calcium/Vitamin D supplements and/or  anti-osteoporotic medication  Polypharmacy (≥ 5 medications) |  | Questionnaire  record | X | X | X | X | X | X | Only baseline and discharge via record |
| Falls and fractures history | N/A | Fall = “an unexpected event in which the patient comes to rest on the ground, floor or lower level” |  | Questionnaire  Record | X | X | X | X | X | X | Only baseline and discharge via record |

M = month, FU = follow-up.

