***Process outcomes in the prospective pre- and post-cohort and retrospective pre-cohort.***

| **Variable** | **Instrument** | **Description** | **Score** | **Type of assessment** | **Prospective pre-cohort/post-cohort** | | | | | | **Retrospective pre-cohort** |
| --- | --- | --- | --- | --- | --- | --- | --- | --- | --- | --- | --- |
|  |  |  |  |  | **Admission** | **Discharge** | **1M FU** | **3M FU** | **6M FU** | **12M FU** | **Yes/No** |
| Reach | NA | Only post-cohort: Number of eligible patients included within G-COMAN | NA | NA |  | X |  |  |  |  | Yes |
| Fidelity | NA | Only post-cohort: Number of patients receiving the core components of G-COMAN | NA | NA |  | X |  |  |  |  | Yes |
| Physical therapy | NA | Number of patients receiving physiotherapy  Numbers of days until start physiotherapy | NA | NA |  | X |  |  |  |  | Yes |
| Dietary advice | NA | Number of patients receiving dietary advice  Number of days until start of dietary advice | NA | NA |  | X |  |  |  |  | Yes |
| Physical restraints | NA | Number of patients being restrained  Duration of the use of restraints  Type of restraints used | NA | NA |  | X |  |  |  |  | Yes |
| Indwelling catheters | NA | Number of patients with an indwelling catheter (urinary tract catheter or intravenous catheter)  Duration of catheterization  Reason for catheterization | NA | NA |  | X |  |  |  |  | Yes |
| Medication reconcilliation | NA | Number of patients with calcium/vitamin D supplements and/or AOM | NA | NA |  | X |  |  |  |  | Yes |
| Referral to geriatric outpatient clinic at discharge | NA | Number of patients referred to the falls clinic, memory clinic, follow up | NA | NA |  | X |  |  |  |  | Yes |
| Referral to FLS | NA | Number of patients referred for Zoledronate infusion or metabolic bone consultation | NA | NA |  | X |  |  |  |  | Yes |

M = months, FU = follow-up.

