### 4.3 Expected duration of trial

Start Oct 2021 with inclusions of first patients in pre-cohort, till March 2022 with 1 year follow-up. Patients in the feasibility study will be recruited before start of the post-cohort and will start whenever the project team is convinced that the G-COMAN program is implemented as wanted. This will preferably be in the timeframe between May - July 2022. Post- cohort patients will be recruited from Sept 2022 onwards to Sept 2023 with again 1 year follow-up

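### Referral and secondary fracture prevention are timed both at discharge and over one year, and the one-year reading does not compare the cohorts on equal terms

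*Protocol*

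**What the plan says.** **Day clinic referral.** Protocol section 3.3 (process outcomes) defines this as "referral to geriatric day clinic (appointment to E459 in the year following first admission". The process-outcomes table in section 3.6 has "Referral to geriatric outpatient clinic at discharge", marked in the discharge column only and available for retrospective controls. Section 5.1 also lists it under the discharge assessment.

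**Fracture liaison.** Within secondary fracture prevention, section 3.3 has "appointment to fracture liaison service (12 months after surgery". As a process outcome in the same section it carries no window. The process table has "Number of patients referred for Zoledronate infusion or metabolic bone consultation", again at discharge and available for retrospective controls.

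**Medication.** Section 3.3 places calcium/vitamin D and osteoporosis treatment within secondary fracture prevention at 12 months. The same section also lists medication reconciliation at admission and discharge. For retrospective controls, the effectiveness table in section 3.6 gives medication as "Only baseline and discharge via record". Section 5.1 says that mortality is the only 12-month item collected retrospectively.

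**Calendar.** Section 4.3 has "Start Oct 2021 with inclusions of first patients in pre-cohort, till March 2022 with 1 year follow-up". The Background says "From 2022 onwards, G-COMAN will start implementing the program on the traumatology ward". Section 4.3 says of the feasibility phase, "This will preferably be in the timeframe between May - July 2022", and starts post-cohort recruitment in September 2022.

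**The concern.** These outcomes show most directly whether care on the ward changed. If the time point is open, two analysts can produce different numerators from the same records, and the choice could be made after the data are seen.

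The one-year reading raises two further problems.

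- **Ascertainment.** Part of the control group cannot supply the 12-month medication component.
- **Exposure.** The year after a control's fracture extends into the period when the programme runs on the same ward. Section 3.4 has the programme nurse screen newly admitted older patients. The components listed in section 3.3 include fracture liaison referral and supplement or osteoporosis prescription at discharge, and these are the events being counted. Readmission and new fracture are themselves endpoints, so the protocol expects some controls to come back. The statement on risk of bias in section 8.2 does not mention this route.

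**Working it through.** **Step 1. The definitions side by side.**

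| Outcome | Section 3.3 | Sections 3.6 and 5.1 | Retrospective controls |
|---|---|---|---|
| Day clinic | Appointment within a year of admission | Referral, at discharge | Yes, in the discharge-timed table |
| Fracture liaison | 12 months (secondary fracture prevention); no window (process outcome) | Referral, at discharge | Yes, in the discharge-timed table |
| Calcium/vitamin D, osteoporosis treatment | 12 months (secondary fracture prevention); admission and discharge (process outcome) | Effectiveness table: every visit to 12 months; process table: discharge | Baseline and discharge only |

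The event counted for the day clinic also shifts, from an appointment to a referral. The index discharge is the one time point for which the tables mark all three outcomes as available in every group.

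**Step 2. Overlap of the control year with the programme.** No figure in the protocol covers this, so it is calendar arithmetic. The inputs are prospective control admissions from 1 October 2021 to 31 March 2022 (section 4.3), assumed evenly spread, and a 365-day window from admission. With A the admission date and L the date from which the programme is counted:

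overlap = (A + 365 days) − max(A, L)

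| L | Basis | Range, days | Mean, days | Mean share |
|---|---|---|---|---|
| 1 Jan 2022 | Earliest reading of the Background | 273–365 | 341.5 | 94% |
| 1 May 2022 | Start of feasibility period | 153–334 | 243.5 | 67% |
| 31 Jul 2022 | End of feasibility period | 62–243 | 152.5 | 42% |
| 1 Sep 2022 | Start of post-cohort | 30–211 | 120.5 | 33% |

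For example, a patient admitted on 1 October 2021 has a window ending 1 October 2022, which is 30 days past 1 September. All prospective controls overlap in every row. Retrospective controls' admission dates and their share of the pre-cohort are not stated, so their overlap cannot be computed.

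**Step 3. What overlap could do to the control rate.** The protocol gives no return or referral rates, so all rates here are assumptions. Suppose 10% to 20% of controls return to the ward, evenly over the year. Suppose referral is 20% per admission under usual care and 50% under the programme. A return changes the result only if the control was not already referred (0.8), and only by the excess over usual care (0.5 − 0.2 = 0.3). The multiplier is 0.8 × 0.3 = 0.24.

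- Low: 0.10 × 0.50 × 0.24 = 1.2 points (50% overlap, from 1 July 2022: 3 to 9 months, mean 6/12).
- High: 0.20 × 0.67 × 0.24 = 3.2 points (67% overlap, from 1 May 2022).
- If half the control group is retrospective with no overlap: 0.6 to 1.6 points.

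**Step 4. Effect on a comparison.** Assume true referral rates of 20% and 40%, and 108 × 0.95 ≈ 103 evaluable per group. If a fraction c of controls is referred at the programme rate, the control rate becomes 0.20 + 0.20c and the difference 20 × (1 − c) points. With d the difference as a proportion and p̄ the mean of the two rates p₁ and p₂:

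power = Φ{[d − 1.96√(2p̄(1 − p̄)/n)] / √([p₁(1 − p₁) + p₂(1 − p₂)]/n)}

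| c | Difference, points | Power |
|---|---|---|
| 0 | 20 | 0.885 |
| 10% | 18 | 0.802 |
| 20% | 16 | 0.695 |
| 30% | 14 | 0.571 |

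The planned 108 per group is not in question here. It rests on in-hospital complications, which are complete before the overlap matters.

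**The case against.** **The definitions can be read together.** A referral made at discharge could be confirmed by an E459 appointment within the year. That is possible, but section 3.3 does not say so. As worded, it counts any appointment in the year, including one that arises from a later admission.

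**Much of the discharge measurement is already planned.** This is correct. The process table and section 5.1 place both referrals at discharge, and medication reconciliation has a discharge time point. The plan therefore needs reconciling, and no new data collection is required.

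**Secondary fracture prevention at 12 months is a separate effectiveness question.** This is fair, and the 12-month values are worth keeping. They still cannot be a like-for-like cohort comparison when retrospective controls have no medication data after discharge.

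**Calendar overlap is not exposure.** This is also correct. A reader might infer that the control arm is contaminated, but the documents do not show it. The programme acts on patients newly admitted to the ward, so the route they describe requires a return to E456. Section 3.4 then screens for eligibility, so not every returning patient need receive the full programme.

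**Retrospective controls do have medication data.** A reader might take them to have none. The protocol provides baseline and discharge values. Only later values are missing, which is a gap in ascertainment and a different matter from contamination.

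**Re-enrolment is speculative.** It requires a new fracture, admission to the ward, eligibility and fresh consent, and no frequency is given. Section 4.2 nevertheless leaves it open.

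**Conclusion.** The contradiction in timing is established from the text and needs resolving. On the one-year reading the 12-month medication component rests on only part of the control group. Every prospective control's window also overlaps the programme period, on average by 33% counted from September 2022 and 67% from May 2022, assuming even accrual.

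Bias from controls returning to the ward is a risk of unknown size, probably towards no difference. A reader could multiply an assumed 10% to 20% return rate by the overlap and a 50% programme referral rate, and report a rise of 2.5 to 6.7 points in control referral (0.10 × 0.50 × 0.5 to 0.20 × 0.67 × 0.5). The documents do not support that as an effect on the control arm. It ignores referrals that would have happened anyway, covers prospective controls only, and rests on rates the protocol does not give. The smaller figures in the working are also illustrations only.

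The matter is confined to secondary and process outcomes. The primary endpoint and the sample size are unaffected.

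**What to change.** 1. Bring section 3.3 into line with the process table in section 3.6. The between-cohort comparison becomes day clinic referral, fracture liaison referral, and calcium/vitamin D or osteoporosis medication status at the index discharge, for all patients including retrospective controls. State whether a referral or an appointment is the event.
2. Keep the 12-month values as descriptive, and state which patients contribute to each component.
3. If return admissions to E456 are handled in the 12-month values, use one rule for both cohorts, for example counting only referrals that arise from the index admission. Removing return-visit referrals from controls alone would favour the programme and should be avoided.
4. Add to section 4.2 that each patient is enrolled once, at the first eligible admission.

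This costs protocol wording, because the discharge data are already planned for every group. The small downside is that referrals first made after the index discharge no longer count in the main comparison, in either cohort. The change concerns when outcomes are measured and does not alter care.

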### 3.4 Trial Design

single-centre pre-post implementation study on the traumatology ward of the University Hospitals Leuven

**Usual care (pre-cohort):** the control group receives usual care on the traumato ward. This means that the patient is cared for by a surgical resident. The interprofessional team furthermore consists of ward nurses, a physiotherapist, an occupational therapist and a social worker. No tailored geriatric protocols are available to the traumato team, except for those that are available hospital-wide for all patients (e.g. fall prevention, delirium). Geriatric expertise is available upon active request by the traumato team and includes the comprehensive evaluation of the patient by a geriatric nurse (consultation model).

Due to the design of the G-COMAN strategic project and its predefined strict timing schedule (a phased implementation with the need of a rapidly full implementation), the timeframe for inclusion of the pre-cohort is limited. At the end of the pre-cohort, the predefined sample size will not be reached. To obtain sufficient included patients in the pre-cohort, this patient cohort will be supplemented with patients of which retrospectively information will be gathered. This results in a pre-cohort that will be partly prospective and partly retrospective.

**Geriatric co-management intervention, quality-improvement project G-COMAN (post-cohort):** A dedicated traumato nurse (G-COMAN nurse) will systematically perform a frailty screening in all newly admitted older patients on the traumato ward to evaluate if they are to be included in the G-COMAN program. In eligible patients, a comprehensive geriatric assessment (CGA) will be performed by the G-COMAN nurse. Based on identified potential problems, a tailored care plan based on predefined geriatric protocols will be launched. As part of the project a geriatric specialist nurse will provide every weekday training and education of the G-COMAN nurse and other team members on the traumato ward. The implementation of automated care plans and predefined geriatric protocols will be coordinated by a G-COMAN project coordinator, as well as the organisation of focus groups and intervisions to ensure smooth and supported collaboration.

In between pre-cohort and post-cohort, a single intervention group will be recruited as part of a feasibility study, in order to evaluate if the intervention is implemented successfully. If this is not the case, the implementation will be adapted and revaluation of successful implementation will be planned.

Due to the nature of the study design, health professionals and patients cannot be blinded. Blinding of outcome assessors is not considered feasible due to limited resources.

### 3.5 Study diagram

###

[figure not shown]

3.6 Trial Flowchart

### *Baseline variables and effectiveness outcomes including time points in the prospective pre- and post-cohort and retrospective pre-cohort.*

| **Variable** | **Instrument** | **Description** | **Score** | **Type of assessment** | **Prospective pre-cohort/post-cohort** | | | | | | **Retrospective pre-cohort** |
| --- | --- | --- | --- | --- | --- | --- | --- | --- | --- | --- | --- |
|  |  |  |  |  | **Admission** | **Discharge** | **1M FU** | **3M FU** | **6M FU** | **12M FU** | **Yes/No** |
| Demographics | N/A | Age, gender |  | Record | X |  |  |  |  |  | Yes |
| Comorbidities | Age-adjusted Charlson Comorbidity Index | Assessment of 16 medical conditions scored based on severity and age | 0-37 | Record | X |  |  |  |  |  | Yes |
| Activities of Daily Living (ADL) | Katz index | Bathing, dressing, toileting, transferring, continence, feeding | 6-18 | Questionnaire | X | X | X | X | X |  | Only baseline via record |
|  | Modified Barthel index | Bowels, bladder, grooming, toilet use, feeding, transfers, mobility, dressing, stairs, bathing | 0-100 | Questionnaire | X | X | X | X | X |  | Only baseline via record |
| Instrumental ADL | Lawton and Brody scale | Telephone use, shopping, food preparation, housekeeping, laundry, mode of transportation, medication use, finances | 0-8 | Questionnaire | X | X | X | X | X |  | Only baseline via record |
| Nutritional status | Mini nutritional assessment | 6 screening questions | 0-14 | Questionnaire | X |  | X | X | X |  | Only baseline via record |
| Mental status | Mini-cog | Three-item word memory and clock-drawing | 0-5 | Test | X | X |  |  |  |  | Only baseline via record |
| Injury and surgery details | N/A | Type of fracture  Type of surgery  Time to surgery  ASA score |  | Record |  | X |  |  |  |  | Yes |
| In-hospital complications | N/A | Delirium  Congestive heart failure  Pneumonia  Deep venous thrombosis  Pulmonary embolism  Myocardial infarction  Urinary tract infection |  | 4AT  Record |  | X |  |  |  |  | Yes, record |
| Length of hospital stay | N/A |  |  | Record |  | X |  |  |  |  | Yes |
|  |  |  |  |  |  |  |  |  |  |  |  |
| Unplanned readmissions | N/A |  |  |  |  |  | X | X |  |  | Yes |
| Mortality | N/A |  |  | Record |  | X | X |  |  | X | Yes |
| Living situation | N/A |  |  | Questionnaire | X | X | X | X |  | X | Only baseline and discharge via record |
| Quality of life | EQ-5D | Mobility, self-care, daily activities, pain, anxiety |  | Questionnaire | X | X | X | X | X | X | No |
| Medication | N/A | Use of calcium/Vitamin D supplements and/or  anti-osteoporotic medication  Polypharmacy (≥ 5 medications) |  | Questionnaire  record | X | X | X | X | X | X | Only baseline and discharge via record |
| Falls and fractures history | N/A | Fall = “an unexpected event in which the patient comes to rest on the ground, floor or lower level” |  | Questionnaire  Record | X | X | X | X | X | X | Only baseline and discharge via record |

M = month, FU = follow-up.

***Process outcomes in the prospective pre- and post-cohort and retrospective pre-cohort.***

| **Variable** | **Instrument** | **Description** | **Score** | **Type of assessment** | **Prospective pre-cohort/post-cohort** | | | | | | **Retrospective pre-cohort** |
| --- | --- | --- | --- | --- | --- | --- | --- | --- | --- | --- | --- |
|  |  |  |  |  | **Admission** | **Discharge** | **1M FU** | **3M FU** | **6M FU** | **12M FU** | **Yes/No** |
| Reach | NA | Only post-cohort: Number of eligible patients included within G-COMAN | NA | NA |  | X |  |  |  |  | Yes |
| Fidelity | NA | Only post-cohort: Number of patients receiving the core components of G-COMAN | NA | NA |  | X |  |  |  |  | Yes |
| Physical therapy | NA | Number of patients receiving physiotherapy  Numbers of days until start physiotherapy | NA | NA |  | X |  |  |  |  | Yes |
| Dietary advice | NA | Number of patients receiving dietary advice  Number of days until start of dietary advice | NA | NA |  | X |  |  |  |  | Yes |
| Physical restraints | NA | Number of patients being restrained  Duration of the use of restraints  Type of restraints used | NA | NA |  | X |  |  |  |  | Yes |
| Indwelling catheters | NA | Number of patients with an indwelling catheter (urinary tract catheter or intravenous catheter)  Duration of catheterization  Reason for catheterization | NA | NA |  | X |  |  |  |  | Yes |
| Medication reconcilliation | NA | Number of patients with calcium/vitamin D supplements and/or AOM | NA | NA |  | X |  |  |  |  | Yes |
| Referral to geriatric outpatient clinic at discharge | NA | Number of patients referred to the falls clinic, memory clinic, follow up | NA | NA |  | X |  |  |  |  | Yes |
| Referral to FLS | NA | Number of patients referred for Zoledronate infusion or metabolic bone consultation | NA | NA |  | X |  |  |  |  | Yes |

M = months, FU = follow-up.

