# Study Synopsis

| Title of clinical trial |  | Geriatrics and traumatology co-managing fragility fractures: effectiveness and success of implementation in a single centre setting |
| --- | --- | --- |
| Protocol Short Title/Acronym |  | G-COMAN FRACTURES |
| Sponsor name |  | UZ Leuven |
| Principal Investigator |  | [name] |
| Medical condition or disease under investigation |  | Older fragility fracture patients |
| Purpose of clinical trial |  | 1) To evaluate the effectiveness of a nurse-led geriatric-traumato co-management program using outcome indicators  2) To evaluate the feasibility of a nurse-led geriatric-traumato co-management program  2.1 To evaluate the reach and fidelity  2.2 To evaluate implementation targets 2.3 To evaluate implementation determinants  3)To evaluate the process of implementation of a nurse-led geriatric-traumato co-management program  3.1 To evaluate the reach and fidelity  3.2 To evaluate process outcomes |
| Primary objective |  | 1) Effectiveness evaluation: To determine if geriatric co-management is superior in preventing in-hospital complications |
| Secondary objective (s) |  | 1) Effectiveness evaluation: To determine if geriatric co-management is superior on following outcome indicators:  - length of stay  - unplanned readmissions within 30 and 90 days  - mortality  - functional status  - nutritional status  - quality of life  - falls and new fracture rate  - Discharge to a higher care level  - secondary fracture prevention started  - Cost-benefit of G-COMAN program  2) feasibility and process evaluation: To evaluate if geriatric co-management was successful implemented on the traumato ward:  -2.1 & 3.1: reach of the program and fidelity towards the core components of the care model  - 2.2: implementation targets  - 2.3: implementation determinants  -3.2: process outcomes:  * time to start physiotherapy  * time to start dietary advice  * use and duration of physical restraints  * use and duration of indwelling catheters (urinary tract catheter or intravenous catheter)  * Medication reconciliation at admission and discharge  * referral to geriatric day clinic  * referral to fracture liaison services |
| Trial Design |  | pre-post implementation study on the traumatology ward of the University Hospitals Leuven. |

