- the fidelity towards the core components of the program (% of included patients who received the core components of the intervention). The core components are 1) the screening questionnaire, 2) comprehensive geriatric evaluation, 3) individual care plan and 4) follow-up.

- The fidelity towards the other intervention components:

- Patient received physiotherapy within 24h postoperative
- The patient was evaluated using the food quadrant method by a logistics employee
- Patient received swallowing screening by a nurse
- If there is no indication for an indwelling catheter, the patient is free of an indwelling catheter
- If a post-void residual volume of ≥ 300 ml is observed in a patient, the residual volume is removed using intermittent catheterization before end of shift after detection of symptoms
- If the urinary catheter was removed, the post-void residual volume is monitored using a bladder scan in the next shift
- If a patient has not passed stool for 3 days, the patient is prescribed oral laxatives before day 4 without stool
- If a patient has not passed stool for 5 days, the patient receives an enema before day 6 without stool
- If there is no indication for a physical restraint, the patients is free of a physical restraint
- If a patient is delirious, the DOS scale was followed up during the next shift
- If a patient reports a pain score of 4 or higher (out of 10), pain medication is given unless refused by the patient within 1h of onset of symptoms
- If a patient reports a pain score of 4 or higher (out of 10), the pain is re-evaluated within 1h of onset of symptoms
- If a patient did not take calcium/vitamin D supplements or anti-osteoporotic medication at admission, it was prescribed at discharge
- The patient was referred to a fracture liaison service

2.2: Implementation targets: awareness, knowledge, motivation to change, perceived acceptability and feasibility, and believe in the benefit, value and success of the program

2.3: Implementation determinants: facilitators and barriers of the program

3. Process evaluation (how well was the process of care changed?)

3.1: reach and fidelity will be reevaluated the same way as expressed above.

3.2: process outcomes

- time to start physiotherapy (as first day after surgery with a first registered contact in electronic patient record)

- % of patients receiving dietary advice and time to start dietary advice

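### The objective is that secondary fracture prevention is started, but no stated between-cohort outcome counts new starts

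*Protocol*

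**What the plan says.** The topic appears in six places in the protocol, in different terms.

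- **Synopsis, secondary objectives:** superiority of co-management on "secondary fracture prevention started".
- **Section 3.3, effectiveness endpoints:** "secondary fracture prevention: documentation of fall risk assessment, medication review of calcium/vitamin D use and osteoporosis treatment, appointment to fracture liaison service", with a 12-month time point.
- **Section 3.3, process outcomes:** "Medication reconciliation at admission and discharge (calcium/vitamin D supplements and AOM"), listed apart from referral to fracture liaison services.
- **Section 3.6, process-outcome table, medication reconciliation row:** "Number of patients with calcium/vitamin D supplements and/or AOM", marked under discharge and available for the retrospective pre-cohort.
- **Section 3.6, effectiveness table, medication row:** "Use of calcium/Vitamin D supplements and/or" anti-osteoporotic medication (AOM), at admission, discharge and each follow-up. For the retrospective pre-cohort it is "Only baseline and discharge via record".
- **Section 3.3, fidelity towards other intervention components:** "If a patient did not take calcium/vitamin D supplements or anti-osteoporotic medication at admission, it was prescribed at discharge".

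Section 8.2 plans univariable tests for secondary outcomes and logistic regression for dichotomous ones. Its only list of adjustment variables belongs to the model for in-hospital complications, and admission medication is not on it.

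**The concern.** Starting prevention is a change between admission and discharge in patients who were not already treated. The section 3.3 endpoint records that a review was documented and an appointment made, and either can happen without anything being started. The medication row of the process table records who has treatment at discharge. A long-term vitamin D user who leaves with the same prescription is counted there in the same way as a patient newly treated.

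The cohorts are not randomised, and section 3.4 makes the pre-cohort partly retrospective. If discharge use is taken as the evidence for the synopsis objective, prescribing from before the fracture is mixed with the programme's effect. A difference between cohorts in admission use would then look like an effect of the programme.

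**Working it through.** **Which measures could carry the objective**

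| Measure | Compared between cohorts? | Counts new starts? |
|---|---|---|
| Section 3.3 secondary fracture prevention endpoint | Yes | No: documentation, review, appointment |
| Medication reconciliation, process table | Yes | No: all users at discharge |
| Medication use, effectiveness table | Yes, at admission and discharge | Not as described, but derivable |
| Fracture liaison referral | Yes | No: a referral |
| Fidelity item on patients without treatment at admission | No comparison stated | Yes |

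**The plan's own figure.** The protocol gives no figure for this outcome. Its 108 per group (section 8.1) concerns complications. It reproduces at 71% versus 51% with a continuity correction: 102 per group, and 102/0.95 = 107.4, rounded up to 108. Nothing below changes it.

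**How a count of all users behaves.** Let b be the share using at admission, all assumed to continue to discharge, and s the start rate among the rest.

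Use at discharge: p = b + (1 − b)s.

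With the same b in both cohorts, the difference is (1 − b)(s₁ − s₀). With the same s but different b, it is (1 − s)(b₁ − b₀), although the programme changed nothing.

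All inputs from here on are assumed.

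*Shrinkage, starts 20% versus 40% (a 20-point difference):*
- b = 30%: 0.3 + 0.7×0.2 = 44%; 0.3 + 0.7×0.4 = 58%; difference 14 points.
- b = 50%: 0.5 + 0.5×0.2 = 60%; 0.5 + 0.5×0.4 = 70%; difference 10 points.
- b = 70%: 0.7 + 0.3×0.2 = 76%; 0.7 + 0.3×0.4 = 82%; difference 6 points.

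*Imbalance, starts 20% in both cohorts, admission use 45% versus 55%:* 0.45 + 0.55×0.2 = 56%; 0.55 + 0.45×0.2 = 64%. That is 8 points with no programme effect.

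*Power, starts 30% versus 50%, 108 × 0.95 ≈ 103 evaluable per group, two-sided 0.05:*

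| b | All users at discharge: difference | Power | New starts among non-users: n per group | Power |
|---|---|---|---|---|
| 0 | 20 points | 84% | 103 | 84% |
| 0.2 | 16 points | 63% | about 82 | 75% |
| 0.4 | 12 points | 43% | about 62 | 62% |
| 0.6 | 8 points | 27% | about 41 | 46% |

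With starts of 40% versus 60% and b = 0.4, the powers are 47% and 61%. In these examples the new-start measure keeps more power despite its smaller denominator.

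**If the and/or is read as one composite.** With supplement use v and AOM use a, assumed independent, the composite is 1 − (1 − v)(1 − a).
- v = 70% in both cohorts, a from 10% to 30%: 1 − 0.3×0.9 = 73%; 1 − 0.3×0.7 = 79%. A 20-point gain in AOM shows as 6 points.
- v from 50% to 70%, a = 10% in both: 1 − 0.5×0.9 = 55%; 1 − 0.3×0.9 = 73%. An 18-point gain appears with no gain in AOM.

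**The case against.** The strongest reply is that the discharge count is not the endpoint for this objective. Section 3.3 lists secondary fracture prevention as a patient outcome and medication reconciliation as a process outcome. This stands. A reader might infer that the fracture-prevention endpoint itself counts anyone on a supplement or AOM and is diluted for that reason. The documents do not support that, because the named endpoint does not count medication users at all. Its mismatch with the synopsis is documentation against initiation.

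A reader might also infer that a supplement alone is declared a success. No passage defines success for the reconciliation row. The and/or may only list what is recorded, and the section 3.3 wording uses a plain conjunction and names both admission and discharge. The composite reading is possible but not established.

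Fracture liaison referral is already compared between cohorts and follows this fracture, so the comparison is not silent on prevention. It still falls short of a start.

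The fidelity item is not expressly confined to the post-cohort. The table's post-cohort-only label sits on a row naming the core components, while this item is listed under other components. The same row also reads Yes for the retrospective pre-cohort. What stands is that no text gives the item a pre-post comparison.

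Finally, admission and discharge use are both recorded, and deriving change could be left to an analysis plan. That would be a fair answer if the protocol were silent. Here it fixes the outcome in several places, in terms that differ and that do not count starts.

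**Conclusion.** The point holds in a limited form. Followed as written, the protocol leaves the synopsis objective without a between-cohort measure of new starts. The nearest medication measure mixes treatment that predates the fracture with treatment begun in hospital.

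The factor (1 − b) is exact algebra, given equal admission use in the cohorts and continuation of all admission users. Its size here is unknown: the protocol gives no admission-use or start rates, so every percentage above other than those behind the 108 is an illustration. The imbalance example likewise shows a mechanism and is not evidence that the cohorts differ.

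The flaw is in the outcome definition and not in the data collection. It concerns a secondary objective and a process outcome. The primary endpoint and the 108 per group are untouched. It is worth correcting because the objective is stated as superiority and the remedy is cheap.

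**What to change.** Reconcile the synopsis objective, the section 3.3 endpoint, the section 3.3 process outcome and the two section 3.6 rows, so that each names the same quantity or is clearly a different one.

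Add one comparative outcome: new prescription between admission and discharge, among patients discharged alive who were not using that class at admission. Report it separately for calcium/vitamin D and for AOM. Keep documented review and fracture liaison referral as separate items. Discharge is the last point at which medication is available for every patient, including the retrospective pre-cohort.

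The cost is wording and a smaller denominator, about 62 instead of 103 per group if 40% were users at admission. No new data are needed, provided the two classes are recorded separately. Which agents count as adequate prevention is for the investigators to decide.
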